### Randomization

After the acquisition of written informed consent, the practitioners who will be performing the intervention will conduct a screening interview. Then, the assessor will perform baseline measurements for participants who meet the inclusion criteria. The 45 enrolled participants will be immediately assigned serial numbers generated using the SPSS version 21 software (IBM Corp., Armonk, NY, USA) and randomly allocated to 1 of the 3 study groups (*n* = 15 per group). The serial number codes will be inserted in opaque envelopes that will be sealed and stored in a double-locked cabinet; these will be opened by the PI or practitioners who will perform the intervention in the presence of the patient and a guardian.

### Implementation

The CRC will generate the allocation sequence, enroll participants, and assign participants to the interventions.

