### Participant recruitment

Participants will be recruited at the DongShin University Gwangju Korean Medicine Hospital, Republic of Korea. The study will be advertised through local newspapers, the Internet, and posters in communities and hospitals. Interested individuals will receive instructions for clinical trial participation through phone calls or visits to our hospital. When interested individuals visit the clinical research center at DongShin University Gwangju Korean Medicine Hospital, they will receive an explanation about the study from the clinical research coordinator (CRC) and will be asked to voluntarily sign an informed consent form prior to participation.

To facilitate participation in the study, the CRC will adjust the treatment and evaluation schedules of each individual participant. Every time the participants visit, the CRC will explain the schedule for the following visit and will remind the participant of the schedule by phone on the day before the appointment. The CRC will continuously monitor the medical condition of the enrolled participants to ensure their adherence to the intervention protocols.

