ILA and EA will be performed with a medical device composed of a combination of a sterile, stainless steel, disposable acupuncture needle (external diameter, 0.3 mm; inner diameter, 0.15 mm; length, 30 mm), optical fiber-coupled laser diode (i.e., 650 nm, InGaAIP; 830 nm, GaAIAs), low-level laser, and electrical stimulator (Ellise; Wontech, Co., Ltd., Daejeon, Republic of Korea) which will be administered (Fig. 3). With participants in the prone position, the needles will be vertically inserted in Shenshu (BL23), Qihaishu (BL24), Dachangshu (BL25), and Huantiao (GB30) [24, 27]. The depth of insertion will be between 9 and 30 mm, depending on the location of the needle [26]. After insertion, the needles will be left in position for 20 min. Manual stimulation will not be used. Participants in the control group will receive sham ILA for 10 min and real EA for 10 min, while those in the 650 and 830 ILA groups will receive real ILA (650 ILA group, 650-nm wavelength; 830 ILA group, 830-nm wavelength) and real EA both for 10 min. Participants will receive treatment once/day, twice/week for 4 weeks. The laser parameters will be as follows: pulse mode, pulse-type wave; output power, 20 mW; frequency, 50 Hz; and irradiated area, 0.15 × 0.15 mm^2^. EA will be applied with a biphasic waveform current, which is a compressional wave that combines an interrupted wave and a continuous wave, in triangular form, at a frequency of 50 Hz [25]. On the basis of the previous RCTs to investigate the efficacy of LLLT on CLBP [13, 19], the control group will undergo the same procedures as the ILA group, but the laser will not be turned on. The acoustic functions of the equipment will be preserved to ensure blinding. No significant differences in observation, feeling, or sound should be found between the 3 groups during the procedure. Hence, all participants will be blinded to the group selection.

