### Incidence of AEs

AEs are undesirable and unintentional signs, symptoms, or diseases that appear during or after treatment in a clinical trial. Participants in this study will be required to voluntarily report any AEs. All AEs that occur during the trial will be documented. AEs that could occur in this study include skin irritation, bleeding, local hematoma, pallor, sweating or dizziness, fainting during acupuncture treatment, continuous severe pain for > 1 h after acupuncture treatment, objective worsening of existing symptoms, and undesirable and unintentional signs, symptoms, or diseases. The CRC will record all AEs in detail, including the time and date of occurrence, degree of severity, any measures related to the treatment of the AE, and any potential causal relationships between the treatment and the AE. All AEs will also be reported to the PI and relevant IRB. In case of SAEs, defined as AEs causing severe disability or malfunction, appropriate measures will be taken, and the incident will be immediately reported to the PI and relevant IRB. In cases in which an AE occurs because of the clinical trial, participants will notify the CRC and PI and will be compensated.

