### Quality assurance

This protocol has been reviewed and revised several times by experts on acupuncture, orthopedics, statistics, and methodology. Before the trial, all the researchers will be requested to attend a series of training sessions, which will ensure that the personnel involved fully understand the trial protocol and standard operating procedures (SOPs) of the study. The data monitoring committee (DMC) will comprise the PI, CRC, and a researcher who will not be involved in the data collection aspect of this study. The DMC, which is independent from the sponsor and free from competing interests, will manage the data to ensure data validity. This study will be monitored by a clinical research associate (CRA), who will check all documents related to this study, including the case report forms (CRFs) and SOPs, and ensure that this clinical trial is conducted in accordance with the prescribed protocols and SOPs. Monitoring will be performed by an independent CRA, who will not be involved in any other aspect of the trial. In the event that the protocol described herein is revised, the revisions will require approval from the Ministry of Food and Drug Safety and the IRB of DongShin University Gwangju Korean Medicine Hospital.

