### Confidentiality and data management

All identification records of the participants will be kept confidential. When the results of the study are published, the identification records will be accessible under IRB approval. All documents related to the trial, including CRFs, will be recorded and labeled with participant identification codes and will not reveal the name of the participants. The serial number codes will be stored in sealed, opaque envelopes and kept in a double-locked cabinet. All participant data will be recorded in Excel files by the CRC. All data will be checked by the CRC and rechecked by a researcher, both of whom will not be included in the data collection phase of the study to ensure the reliability of the data. Continuous data will be coded as data values, and categorical data will be coded as number sets for each item by a statistician not involved in the data collection phase of this clinical trial. The data entry and coding will be double-checked. Electronic data will be stored on a password-protected computer. Anyone who is not approved by the IRB will not be able to access the data. In addition, raw data (CRFs) will be stored in a cabinet until the end of the study. Written informed consent for the publication of the individual details and accompanying images will be obtained from the participants.

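### The coordinator who enrols participants also generates the allocation sequence, so sealed envelopes cannot conceal it; opening them before the patient puts blinding at risk unless the slip is uninformative

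*Protocol article*

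**What the plan says.** The Implementation section is one sentence: "The CRC will generate the allocation sequence, enroll participants, and assign participants to the interventions". The CRC also has direct contact with candidates. Under Participant recruitment, when candidates visit the research centre, "they will receive an explanation about the study from the clinical research coordinator (CRC"), and they are then asked to sign the consent form.

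The Randomization section describes the rest of the path to allocation. After consent, "the practitioners who will be performing the intervention will conduct a screening interview", and the assessor then takes baseline measurements. Serial number codes are kept in sealed opaque envelopes in a locked cabinet, and "these will be opened by the PI or practitioners who will perform the intervention in the presence of the patient and a guardian".

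The trial is described as patient-blinded by means of a sham laser. The Interventions section sets out the safeguards (identical procedure with the laser off, device sounds kept, no intended difference in what the patient sees, feels or hears) and concludes: "Hence, all participants will be blinded to the group selection". The Blinding section nevertheless refers, in one sentence, to participants as well as practitioners being unblinded.

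On data handling, Incidence of AEs says "The CRC will record all AEs in detail", while Confidentiality and data management says "All data will be checked by the CRC and rechecked by a researcher, both of whom will not be included in the data collection phase".

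**The concern.** Concealment means that nobody who can influence whether or when a candidate enters knows the next allocation. Here the role that meets candidates and enrols them is also the role that wrote the list. Foreknowledge could affect who is encouraged to join and in what order, and with 15 per arm a few steered entries can unbalance the groups. Selection of this kind cannot be removed by analysis.

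The primary endpoint is a self-marked pain VAS at the end of the intervention, so it is also sensitive to patients knowing whether the laser is on. Opening the envelope in front of the patient creates an opportunity for disclosure that the sham procedure does not cover, because the sham acts later, during treatment.

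**Working it through.** 1. The plan's own figure. Sample size estimation takes a pilot minimum of about 12 per arm and 20% dropout: 12 / (1 − 0.20) = 15 per arm, and 3 × 15 = 45. This reproduces the stated size. The present point does not dispute it; 45 is simply the number of allocations to be concealed.

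2. Who does what, side by side.

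| Step | Role | Section |
|---|---|---|
| Generate sequence | CRC | Implementation |
| Explain study before consent | CRC | Participant recruitment |
| Screening interview | Treating practitioners | Randomization |
| Baseline measures | Assessor | Randomization |
| Enrol | CRC | Implementation |
| Assign | CRC | Implementation |
| Open envelope | PI or treating practitioners | Randomization |

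Generation, enrolment and assignment fall to one role, and no section separates them. The last two rows leave open whether assignment is an act of the CRC or of whoever opens the envelope.

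3. How much the enrolling role could know.
- Holder of the list: 45 of 45 allocations (100%).
- Blind guessing among three equal arms: 45 × 1/3 = 15 of 45 (33%).
- Guessing the arm with most places left: on average 19.65 of 45, and 19.65 / 45 = 43.7%, from 20,000 simulated random lists. This assumes one fixed 15/15/15 list without blocks and a guesser who sees every past allocation.

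The CRC's possible advantage over blind guessing is therefore 45 − 15 = 30 allocations, and over informed guessing 45 − 19.65 = 25.35. These are upper limits on what could be known, not a statement of what was known or used.

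4. Envelope opening. There are two cases. If the slip names the arm, or carries a code the patient or guardian can read, the blinded party may learn the allocation before the first treatment. If the slip carries a code with no meaning to them, opening it in front of them discloses nothing. The article says the envelopes hold serial number codes and does not say which case applies. Whoever delivers treatment must learn the arm from somewhere, and the envelope is the only vehicle described.

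5. Wording conflicts. The Blinding section both sets up a patient-blinded procedure and counts participants among the unblinded; the Interventions section says all participants are blinded. Recording AEs, with time, severity and possible causal relationship, is data collection, so the CRC cannot both do it and be outside the data collection phase.

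**The case against.** Several things can be said for the plan. Practitioners, not the CRC, conduct the screening interview, which narrows the CRC's described control over eligibility, and the article does not name who takes consent. Consent, screening and baseline all precede allocation. An assessor whose only contact with participants is at assessment makes the measurements. The CRC may assign from the list while another person opens the envelope, so the two sections on assignment may be unclear rather than contradictory. The reference to unblinded participants may be a slip of wording. The article itself says the sample is too small to determine efficacy. All of this is fair, but none of it hides the list from the role that wrote it and meets the candidates. That arrangement is stated text, not a detail the article left to a fuller protocol.

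Stronger readings are tempting, and the article does not support them:

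- A reader might infer that patient blinding is unprotected. The envelopes are said to hold codes, no section says that the slip names the arm, and the sham safeguards are real. Only a conditional risk follows.
- A reader might infer that the monitoring committee contradicts its own description, since "The data monitoring committee (DMC) will comprise the PI, CRC, and a researcher who will not be involved in the data collection aspect". The independence claimed is from the sponsor, and PI or CRC membership does not by itself contradict that. The committee also has no bearing on concealment.
- A reader might infer that the CRC judges AE causality knowing the arm. The article says that the CRC records possible causal relationships, and that AEs also go to the PI and the IRB; it does not say who judges.
- A reader might want the bias in millimetres of VAS. The article supplies nothing from which to derive it.

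**Conclusion.** The point holds for concealment, and it is serious there: as written, one role generates the sequence, enrols and assigns, so advance knowledge is possible for all 45 allocations. This rests on taking the Implementation sentence at face value and on the CRC's pre-consent contact with candidates. It does not assume that anyone acted on the knowledge.

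For blinding, the point is conditional: opening the envelope before the patient threatens the blind only if the slip is informative, which the article does not settle. Who assigns is unclear, and the statements on unblinded participants and on the CRC's part in data collection need reconciling. The effect on the primary outcome cannot be quantified, and no sample-size figure changes.

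**What to change.** In the plan, and in any successor trial built on this pilot:

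- Have an existing project member with no participant contact and no part in the final analysis generate the list and seal the envelopes. The researcher outside data collection named under Quality assurance is a candidate. The analysing statistician is not, because the Blinding section keeps that person out of design and execution. The CRC then only enrols.
- Have the treating practitioner open the envelope out of sight of the patient and guardian, and remove the wording that has them present.
- Reconcile Randomization with Implementation on who assigns, the Blinding section with itself and with Interventions on participant blinding, and Incidence of AEs with Confidentiality and data management on the CRC's role.

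Trial status says that recruitment ended on September 17, 2020, so reassigning tasks can no longer help this trial. What remains is disclosure. The report should state who generated, held and opened the allocations and whether the slip revealed the arm. If the steps were carried out as written, it should not claim concealed allocation, and it should claim secured patient blinding only if the slip did not reveal the arm.

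The cost is a short passage in the report and corrected wording; for a later trial, a reassignment of tasks among existing staff.

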### Blinding

Owing to the nature of LA treatment, a double-blind study design cannot be adopted. Therefore, we will adopt a patient-blinded trial procedure using sham LA. During the course of this clinical trial, the assessor will have no contact with the participants other than at the time of assessment. Furthermore, unblinding will not be permitted under any circumstances. However, if an SAE occurs, unblinding will be permitted after an agreement between all the researchers involved. To prevent selection, performance, and attrition biases due to the unblinded participants and practitioners, this study will only involve individuals without conflicts of interest or preconceived positions. All the practitioners who will perform the interventions will receive training in clinical trials before participation. A statistician not involved in the design or execution of the clinical trial will analyze the final data.

### Interventions

The treatment will be administered by Korean medical doctors with 6 years of formal university training in Korean medicine and a license to administer treatments. To ensure strict adherence to the study protocol, the practitioners who will perform the interventions will undergo training together and use the same techniques (Table 1).

**Table 1 Tab1:** Revised Standards for Reporting Intervention in Clinical Trials of Acupuncture (STRICTA)

	Item criteria	Description
1. Acupuncture rationale	1a) Style of acupuncture	Korean medicine therapy
	1b) Reasoning for treatment provided—based on historical context, literature sources, and/or consensus methods, with references where appropriate	1) Discussion among four doctors that practice Korean medicine (consensus) 2) Textbook of acupuncture and moxibustion medicine 3) Relevant articles [13, 14, 19, 24, 25] Selection of treatment regions based on textbooks, related papers, and expert discussions
	1c) Extent to which treatment varied	Standardized treatment
2. Details of needling	2a) Number of needle insertions per subject per session (mean and range where relevant)	8
	2b) Names (or location if no standard name) of points used (unilateral/bilateral)	BilateralShenshu (BL23), Qihaishu (BL24), Dachangshu (BL25), and Huantiao (GB30)
	2c) Depth of insertion, based on a specified unit of measurement or a particular tissue level	The depth of insertion will be 9–30 mm, depending on the location of the needle [26]. After insertion, the needles will be left in position for 20 min.
	2d) Responses sought	No de qi or muscle twitching—only sensation due to needle insertion
	2e) Needle stimulation	650-nm invasive laser, 830-nm invasive laser, and electrical stimulation
	2f) Needle retention time	20 min per session
	2 g) Needle type	Sterile, stainless steel, disposable acupuncture needle (external diameter, 0.3 mm; inner diameter, 0.15 mm; length, 30 mm) consisting of an optical fiber-coupled laser diode (i.e., 650 nm, InGaAIP; 830 nm, GaAIAs) and low-level laser
3. Treatment regimen	3a) Number of treatment sessions	8
	3b) Frequency and duration of treatment sessions	Once/day, twice/week for 4 weeks, 20 min per session
4. Other treatment components	4a) Details of other interventions administered to the acupuncture group	Participants in the control group will receive sham ILA for 10 min and real electroacupuncture (EA) for 10 min, while those in the 650 and 830 ILA groups will receive real ILA (i.e., 650 ILA group, 650-nm wavelength; 830 ILA group, 830-nm wavelength) for 10 min and real EA for 10 min.
	4b) Setting and context of treatment—including instructions to practitioners and information and explanations given to patients	Practitioner-patient conversation about the context of the treatment, life habits, and daily life management
5. Practitioner background	5a) Description of the participating acupuncturists	Korean medicine doctor with the following qualifications: 6 years of formal university training in Korean medicine and a license
6. Control or comparator interventions	6a) Rationale for the control or comparator in the context of the research question, with sources that justify the choice	○ Glazov G, Yelland M, Emery J. Low-dose laser acupuncture for non-specific chronic low back pain: a double-blind randomized controlled trial. J. Acupunct Med. 2014;32:116–123. ○Glazov G, Yelland M, Emery J. Low-level laser therapy for chronic non-specific low back pain: a meta-analysis of randomized controlled trials. J. Acupunct Med. 2016;34:328–341. ○Hwang MS, Heo KH, Cho HW, Shin BC, Lee HY, Heo I, Kim NK, Choi BK, Son DW, Hwang EH. EA as a complement to usual care for patients with non-acute pain after back surgery: a study protocol for a pilot randomized controlled trial. BMJ Open. 2015;5:e007031.
	6b) Precise description of the control or comparator; details for items 1–3 above with the use of sham acupuncture or any other type of acupuncture-like control	Participants in the control group will receive sham ILA for 10 min and real EA for 10 min, while those in the 650 and 830 ILA groups will receive real ILA (i.e., 650 ILA group, 650-nm wavelength; 830 ILA group, 830-nm wavelength) for 10 min and real EA for 10 min. The laser parameters will be as follows: pulse mode, pulse-type wave; output power, 20 mW; frequency, 50 Hz; and irradiated area, 0.15 × 0.15 mm^2^. EA will be applied with a biphasic waveform current, which is a compressional wave that combines an interrupted wave and a continuous wave, in triangular form, at a frequency of 50 Hz [25]. Sham ILA will be applied without any laser power output.

ILA and EA will be performed with a medical device composed of a combination of a sterile, stainless steel, disposable acupuncture needle (external diameter, 0.3 mm; inner diameter, 0.15 mm; length, 30 mm), optical fiber-coupled laser diode (i.e., 650 nm, InGaAIP; 830 nm, GaAIAs), low-level laser, and electrical stimulator (Ellise; Wontech, Co., Ltd., Daejeon, Republic of Korea) which will be administered (Fig. 3). With participants in the prone position, the needles will be vertically inserted in Shenshu (BL23), Qihaishu (BL24), Dachangshu (BL25), and Huantiao (GB30) [24, 27]. The depth of insertion will be between 9 and 30 mm, depending on the location of the needle [26]. After insertion, the needles will be left in position for 20 min. Manual stimulation will not be used. Participants in the control group will receive sham ILA for 10 min and real EA for 10 min, while those in the 650 and 830 ILA groups will receive real ILA (650 ILA group, 650-nm wavelength; 830 ILA group, 830-nm wavelength) and real EA both for 10 min. Participants will receive treatment once/day, twice/week for 4 weeks. The laser parameters will be as follows: pulse mode, pulse-type wave; output power, 20 mW; frequency, 50 Hz; and irradiated area, 0.15 × 0.15 mm^2^. EA will be applied with a biphasic waveform current, which is a compressional wave that combines an interrupted wave and a continuous wave, in triangular form, at a frequency of 50 Hz [25]. On the basis of the previous RCTs to investigate the efficacy of LLLT on CLBP [13, 19], the control group will undergo the same procedures as the ILA group, but the laser will not be turned on. The acoustic functions of the equipment will be preserved to ensure blinding. No significant differences in observation, feeling, or sound should be found between the 3 groups during the procedure. Hence, all participants will be blinded to the group selection.

